##### 2.3.1.1. ITQ-Administered Pre- and Posttreatment

The ITQ is a self-report measure designed to assess symptoms of PTSD and complex PTSD (CPTSD) as defined by the ICD-11 [36]. This questionnaire focuses on core PTSD symptoms such as re-experiencing, avoidance, and a sense of current threat, as well as disturbances in self-organization, including affective dysregulation, negative self-concept, and difficulties in relationships. The tool has a good level or factor structure in Ethiopia [37].

##### 2.3.1.2. GAD-7-Administered Pre- and Posttreatment

The GAD-7 is a widely used self-report tool for assessing the severity of generalized anxiety symptoms. Participants will complete the GAD-7 at baseline and postintervention to evaluate changes in anxiety levels resulting from the TSR intervention. The tool has a good level or factor structure in Ethiopia [38].

##### 2.3.1.3. PHQ-9-Administered Pre -and Posttreatment

The PHQ-9 is a validated tool used to measure the severity of depressive symptoms. This self-report measure will be administered at both baseline and postintervention to assess changes in depression levels among participants. The tool has a good level or factor structure in Ethiopia [39].

##### 2.3.1.4. The EQ-5D-5L Health Questionnaire

The EQ-5D-5L Health Questionnaire is a standardized instrument used to measure health-related quality of life. It includes five dimensions: mobility, self-care, usual activities, pain/discomfort, and anxiety/depression, each with five levels of severity. Participants will complete the EQ-5D-5L at baseline and postintervention to assess changes in their overall health status [40].

##### 2.3.1.5. The OSSS-3

The OSSS-3 is a brief, three-item questionnaire designed to assess the level of social support available to participants. Social support is a critical factor in coping with chronic health conditions and is expected to be significantly impacted by the TSRP intervention. The OSSS-3 will be used at baseline to measure participants' perceived social support.

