**Summary**

• The Traumatic Stress Relief (TSR) program addresses a critical gap in mental health support for individuals affected by leprosy, a population often marginalized and overlooked in healthcare systems.• By implementing a peer-supported group therapy model in Addis Ababa, Ethiopia, this research provides a scalable framework for improving psychological well-being among leprosy patients.• The program not only targets symptoms of posttraumatic stress disorder (PTSD), anxiety, and depression but also aims to reduce stigma and enhance social support networks within the community.• The impact of this research extends beyond immediate health benefits; it has the potential to inform public health policies and practices at local, national, and international levels.• By demonstrating the effectiveness of community-based mental health interventions, the TSR program can influence policymakers to adopt similar approaches for other neglected diseases and vulnerable populations.• Finally, the findings of this study may inspire further peer-supported strategies, fostering a more integrated approach to healthcare that recognizes the importance of mental health alongside physical health.

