### 2.3. Data Collection

#### 2.3.1. Outcomes

The primary outcomes will be the changes in PTSD, anxiety, and depression symptoms, and levels of social support from baseline to postintervention. Secondary outcomes will include participant satisfaction and insights derived from the qualitative data.

Participants will complete a battery of self-report questionnaires at three time points: baseline (T0), postintervention (T1), and at a 1-month follow-up. The assessment includes the International Trauma Questionnaire (ITQ), Generalized Anxiety Disorder 7-item scale (GAD-7), PHQ-9, Health Questionnaire (EQ-5D-5L), the Oslo Social Support Scale (OSSS-3), and 5-Question Stigma Indicator—Affected People.

In addition to the quantitative assessments, a qualitative component will be included postintervention. Semistructured interviews will be conducted with participants from both the intervention and control groups to explore their experiences and views regarding the TSR intervention and standard care, respectively. This qualitative data will provide deeper insights into the feasibility, acceptability, and effectiveness of the intervention.

The sociodemographic questionnaire will collect essential background information about the participants, including age, gender, marital status, education level, employment status, and duration of leprosy diagnosis. These data are crucial for understanding the context in which participants live and how various demographic factors might influence their mental health outcomes. The sociodemographic information will help in identifying potential correlations between participants' backgrounds and their responses to the intervention, ensuring that any observed effects are appropriately contextualized.

The quantitative data will be analyzed using intention-to-treat principles, with comparisons between the intervention and control groups, whereas the qualitative data will be analyzed using the reflexive thematic analysis [32–35].

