##### 2.3.1.6. The 5-Question Stigma Indicator

The tool is used to measure the level of stigma experienced by individuals affected by leprosy. This brief questionnaire will be administered to assess the perceived stigma before the TSR intervention.

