## Figures and Tables

**Table 1 tab1:** Design of the planned intervention.

	Study period			
	Enrollment	Baseline assessment	The intervention	Postintervention assessment
	−*t*1	*t*0	4 sessions	*t*1
Enrollment:				
Eligibility screen	X			
Informed consent	X			
Intervention: TSR				
Assessments:				
Sociodemographic Questionnaire		X		
International Trauma Questionnaire (ITQ)		X		X
Generalized anxiety disorder 7-item (GAD-7)		X		X
Patient Health Questionnaire-9 (PHQ-9)		X		X
Health Questionnaire (EQ-5D-5L)		X		X
Oslo Social Support Scale (OSSS-3)		X		
5-Question stigma indicator—affected people		X		
TFA Acceptability Questionnaire				X
Qualitative interview				X

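### Change in social support is a primary outcome, but the protocol contradicts itself on whether the OSSS-3 is given after baseline

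*Protocol article*

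**What the plan says.** Section 2.3.1 (Outcomes) of the protocol article defines the endpoints: "The primary outcomes will be the changes in PTSD, anxiety, and depression symptoms, and levels of social support from baseline to postintervention". It then sets the timing: "Participants will complete a battery of self-report questionnaires at three time points: baseline (T0), postintervention (T1), and at a 1-month follow-up". The instruments listed for that battery end with "the Oslo Social Support Scale (OSSS-3), and 5-Question Stigma Indicator—Affected People".

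Two other places give a different schedule for the same scale.

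- Section 2.3.1.5 states: "The OSSS-3 will be used at baseline to measure" participants' perceived support. No second administration is mentioned, although the same short section says that the intervention is expected to affect social support.
- In Table 1, the row that begins "Oslo Social Support Scale (OSSS-3" has one mark, under t0, and none under t1.

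The stigma indicator follows the same pattern. Section 2.3.1 includes it in the three-time-point battery. Section 2.3.1.6 says that it "will be administered to assess the perceived stigma before the TSR intervention", and Table 1 marks it at t0 alone. Stigma appears in neither the primary nor the secondary outcomes.

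Section 2.4 (Data and Management) plans a repeated measures analysis of variance on all outcome tools, and says that means, SDs and effect sizes will inform the sample size of a definitive trial.

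**The concern.** A change outcome needs a measurement at both ends of the interval. Field staff usually work from the schedule table. If they follow Table 1 here, the OSSS-3 is collected once, and by section 2.1 baseline assessment comes before randomization. A single pre-randomization score describes the sample but carries no information about the effect of the intervention.

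The trial would then be unable to report one of its own primary outcomes, or to supply the variability and effect size for social support that the definitive trial is meant to use. An analysis plan cannot repair this later: scores not collected at the end of the intervention cannot be recovered, and asking participants to recall them is a different measurement.

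**Working it through.** No sample size, power or alpha figure bears on this point. The check is a count of planned administrations per instrument in each place that states one.

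| Instrument | Section 2.3.1 (battery) | Instrument's own section | Table 1 |
|---|---|---|---|
| ITQ | T0, T1, 1 month | before and after treatment | t0, t1 |
| GAD-7 | T0, T1, 1 month | before and after treatment | t0, t1 |
| PHQ-9 | T0, T1, 1 month | before and after treatment | t0, t1 |
| EQ-5D-5L | T0, T1, 1 month | baseline and after the intervention | t0, t1 |
| OSSS-3 | T0, T1, 1 month | baseline | t0 |
| Stigma indicator | T0, T1, 1 month | before the intervention | t0 |

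**Step 1: what the outcome needs.** For each participant, change = OSSS-3 at T1 − OSSS-3 at T0. That takes two administrations. A repeated measures analysis also needs at least two.

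**Step 2: what each reading supplies.**

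- Section 2.3.1 governs: 3 administrations. Change is computable for every participant retained to T1, up to 100.
- Section 2.3.1.5 and Table 1 govern: 1 administration. Change is computable for 0 of 100, whatever the retention.

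**Step 3: is any other primary outcome affected?** The primary outcomes are PTSD, anxiety, depression and social support, so four. The ITQ, GAD-7 and PHQ-9 have 2 administrations under Table 1 and 3 under section 2.3.1, so their change scores can be computed on either reading. Only social support, 1 of 4, depends on which passage governs.

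**Step 4: could a mark have been lost from the table?** That is unlikely to be the explanation. The prose makes the same split as the table: the first four instruments are described as given before and after, the last two as given before. Two separate places agree with each other against section 2.3.1.

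**Step 5: stigma.** The timing contradiction is the same: 3 administrations against 1. The consequence differs, because no declared outcome rests on the indicator.

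**The case against.** The strongest reply is that section 2.3.1 already schedules the OSSS-3 at all three time points, so the outcome is computable as planned and the other two places are loosely worded. The scale's section does not say that it is given at baseline and never again. Table 1 is also incomplete as a schedule: it has no column for the 1-month follow-up, so a missing mark in it is weak evidence of intent. This stands in part. A reader might infer that the OSSS-3 is definitely given once and that the primary outcome is already lost; the documents do not support that. They support a contradiction, with loss of the outcome on one of two readings. The reply does not remove the contradiction, since the prose and the table agree with each other.

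A reader might also infer that stigma suffers the same loss. It does not. The Summary says that the program "also aims to reduce stigma and enhance social support networks within the community", but that describes the program rather than a trial endpoint. The Introduction's effectiveness objective is limited to PTSD, anxiety and depression. A baseline-only stigma score is a legitimate sample descriptor. Nor does it follow that social effects would go wholly unexamined, since the interviews ask about the reactions of people around the participant. That does not replace a quantitative primary outcome.

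Finally, the trial is exploratory and its Stop-Go rule rests on retention and recruitment, not on the OSSS-3. That is correct: the feasibility decision is untouched. It does not excuse uncertainty over whether a declared primary outcome will be measured.

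**Conclusion.** The point holds as an internal contradiction. Section 2.3.1 makes "levels of social support from baseline to postintervention" part of a primary change outcome and schedules its scale three times; section 2.3.1.5 and Table 1 schedule it once. If the latter two govern, 1 of 4 primary outcomes has no postintervention value, and its change score and repeated measures analysis cannot be computed. If section 2.3.1 governs, nothing is lost. The documents do not say which takes precedence.

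The conclusion assumes that the OSSS-3 is the only measure of social support (no other is named) and that no unseen document already fixes the timing. Because the data cannot be recovered afterwards, the OSSS-3 timing must be settled before the first postintervention assessment. The stigma timing is a minor inconsistency and would not by itself require an amendment of the same urgency.

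**What to change.** Make section 2.3.1, section 2.3.1.5 and Table 1 agree, in one of two ways.

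1. **Keep the outcome.** Mark the OSSS-3 at t1 in Table 1 and reword section 2.3.1.5 to say that it is given at baseline and postintervention. If the 1-month visit is kept, add a column for it to Table 1 and mark the scale there too. The cost is three questions per participant at each existing visit: 3 for t1 alone, 2 × 3 = 6 with the follow-up. The document change is one table and one sentence.
2. **Drop the outcome.** Remove social support from the primary outcomes in section 2.3.1, take the OSSS-3 out of the repeated battery, and present it as a baseline descriptor. This adds no questions, but the trial then gives no quantitative estimate of change in social support.

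Option 1 is cheap and keeps the declared outcome.

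For the stigma indicator, state one timing in sections 2.3.1 and 2.3.1.6 and in Table 1. If it stays at baseline only, remove it from the three-time-point battery and do not claim that the trial tests stigma reduction quantitatively. The description of the program's aims can remain.

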##### 2.3.1.6. The 5-Question Stigma Indicator

The tool is used to measure the level of stigma experienced by individuals affected by leprosy. This brief questionnaire will be administered to assess the perceived stigma before the TSR intervention.

##### 2.3.1.7. The Theoretical Framework of Acceptability (TFA)

The questionnaire is designed to assess participants' perceptions of the acceptability of the TSR intervention. This measure will be administered postintervention to gather feedback on various aspects of the program, including its content, delivery, and perceived effectiveness [41]. The TFA questionnaire will help the research team understand how well the intervention was received by the participants, which is crucial for refining the program and planning future implementations.

##### 2.3.1.8. Feasibility and Acceptability Indicators

The study will monitor the recruitment rate, including the number of patients referred and the proportion who consented out of all eligible individuals with leprosy referred from recruitment sites or through self-referrals, as well as the attrition rate, which is the number of participants withdrawn compared to those who consented.

The study will evaluate the feasibility of administering the baseline and outcome exploratory assessment battery, focusing on randomization, blinding procedures, and the ability to perform a sample size calculation based on the feasibility data.

The evaluation will assess the number of participants recruited and randomized, session attendance, reported adverse effects, assessment measure acceptability, and the potential for future site. Acceptability will be measured using the TFA scale [41, 42], assessing researchers' and participants' perceptions of the intervention's appropriateness.

##### 2.3.1.9. Postintervention Interviews

Finally, upon completion of the TSR intervention, 20 participants will be invited to participate in one-to-one semistructured qualitative interviews. These interviews will explore participants' experiences with the intervention, including their thoughts on the content, delivery, usefulness, acceptability of the sessions, and the changes in the mental health and life related to their participation in the program. The interviews will also investigate barriers and facilitators to implement, offering insights into both successes and challenges. In addition, participants who withdrew or dropped out of the study will also be invited to share their concerns and perceived barriers to participation. All interviews will be audio-recorded and analyzed using the reflexive thematic analysis, providing a comprehensive understanding of the participants' perceptions that complements the quantitative data. Please see sample questions:

Questions for participants are as follows:1. In what way did the TSR sessions impact your life?2. Would you recommend any changes to the TSR sessions?3. What was the reaction of the people around you to your attending TSR sessions?4. Have you faced any challenges while taking part in the intervention?5. Would you recommend TSR to friends or family in the same situation as you?6. Is there any part of the intervention you are not happy with?7. What aspect of the intervention/activities did you find most helpful?8. What were the most important reasons for you to stop (or continue) attending the sessions?9. In what way did the TSR sessions work (or not work) well for you?

### 2.4. Data and Management

Summary statistics, means, medians, counts, and percentages along with corresponding measures of variability will be reported, along with 95% confidence intervals. The information gathered on the variability of the outcome measures will be sufficient to allow a formal sample size calculation to be made for the subsequent definitive RCT. The proportion of participants recruited and retained in the study will be reported along with 95% confidence intervals. A sample size of 100 will allow the recruitment/retention rates to be estimated with an accuracy of ± 8%.

One-way repeated measures analysis of variance to elucidate the impact of interventions on scores on all outcome tools while accounting for baseline characteristics of participants such as age, gender, and baseline severity of psychological symptoms will be employed. Mean and SD and effect sizes calculated as Cohen's d noted in this trial will inform sample size calculation for future definitive trials. The project will also have a clear Stop-Go criterion:• If the retention rate is 70% or higher, we will proceed with the full RCT as it is feasible.• If the retention rate is between 50% and 70%, we will explore methods to increase the retention rate to the required 70%. Alternatively, we may increase the required sample size to account for the higher drop-out rate.• However, if the recruitment rate is less than 50%, a full trial may not be feasible. In such cases, alternative approaches will be considered.

Subgroup analysis will be carried out with respect to age, duration of illness, number of previous episodes, and gender by adding a treatment with covariate interaction into the primary analysis model.

Data will be initially stored in a secured office location and subsequently digitized for storage on a secure network. In addition, all project-generated data will be assigned unique codes to protect participant confidentiality. Data associated with these codes and any identifiable information will be stored separately.

Descriptive statistics will be conducted for baseline and postintervention measures, including mean scores, standard deviations, and ranges. In addition, recruitment, attendance, and dropout rates will be reported to assess feasibility and acceptability.

The interviews will be audio-recorded and transcribed verbatim. To ensure anonymity, all identifying information will be removed and replaced with generic descriptors. Thematic analysis will be used to analyze the data, following its core principles, meaning data saturation will not be considered [33]. Instead, the consolidated criteria for reporting the qualitative research will be applied to enhance transparency in data analysis [43].

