### 2.1. Study Design

This randomized controlled trial (RCT) with a qualitative component is designed to assess the effectiveness of the TSR intervention for individuals affected by leprosy in Addis Ababa, Ethiopia.

Methodological features of this feasibility RCT will minimize the possible bias in the intervention group. These features include allocation concealment (that will be ensured by randomization to be performed by an independent, off-site statistician), blinding (study statistician and the research team carrying out follow-up assessments will be masked to treatment allocation), use of intention-to-treat analysis, and the use of primary versus secondary endpoints.

The study will involve two arms: an intervention group receiving the TSR intervention and a waitlist control group. Participants will undergo individual randomization conducted by an off-site statistician. A total of 100 participants will be randomized in a 1:1 ratio into either the TSR intervention group (*n* = 50) or the waitlist control group (*n* = 50). Randomization will occur after baseline assessments using a computer-generated sequence to ensure allocation concealment.

As this study first of its kind and aims to demonstrate a trend in favor of the intervention and the recruitment and retention of participants into the study, the sample size was informed by community consultation and trial guidelines [20–25] to ensure a sample that allows for the estimation of recruitment and retention parameters, as well as potential effectiveness.

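### The ±8% precision claimed for 100 participants does not hold for retention in the 50–70% band of the Stop-Go rule (±9.8 points at 50%, ±9.0 at 70%); for recruitment it is conservative

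*Protocol article*

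**What the plan says.** Section 2.1 fixes the size of the trial: "A total of 100 participants will be randomized in a 1:1 ratio", 50 per arm. It says the number was informed by community consultation and trial guidelines, "to ensure a sample that allows for the estimation of recruitment and retention parameters" as well as potential effectiveness.

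Section 2.4 then gives the precision: "A sample size of 100 will allow the recruitment/retention rates to be estimated with an accuracy of" ±8%. The sentence before it sets the scale for that figure: "The proportion of participants recruited and retained in the study will be reported along with 95% confidence intervals". No expected retention or recruitment rate accompanies the ±8%.

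The retention rates named in the article are those of the Stop-Go rule in the same section. The upper one is "If the retention rate is 70% or higher, we will proceed with the full RCT as it is feasible". The middle band is "If the retention rate is between 50% and 70%, we will explore methods to increase the retention rate to the required 70"%. The third bullet, which says a full trial may not be feasible, is worded in terms of a recruitment rate below 50%.

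Section 2.3.1.8 defines the recruitment rate as "the proportion who consented out of all eligible individuals with leprosy referred from recruitment sites or through self-referrals". The same section sets attrition as withdrawals relative to those who consented.

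**The concern.** The half-width of a confidence interval for a proportion depends on the proportion. A precision quoted without a rate is normally read as holding whatever the rate turns out to be, or at least over the range that matters for the decision. For retention, that range is around 50% to 70%, and with 100 people a 95% interval there is wider than ±8 points.

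The ±8% is the only number in the article that shows what 100 participants deliver on the feasibility aims. A reader planning the definitive trial would take from it a slightly tighter picture of retention than the data can give. The sentence also applies one figure to two rates that do not share a denominator.

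**Working it through.** **Inputs.** n = 100 randomised (sections 2.1 and 2.4); 95% two-sided intervals (section 2.4); retention rates of 70% and 50% (Stop-Go rule, section 2.4); recruitment denominator = eligible people referred, number not stated (section 2.3.1.8).

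**Can ±8% be reproduced?** The half-width is h = 1.96 × √(p(1 − p)/n). Setting h = 0.08 and n = 100 gives p(1 − p) = 100 × (0.08/1.96)² = 0.1666, so p = 0.5 ± √(0.25 − 0.1666), that is 0.789 or 0.211. The figure therefore holds for rates of about 79% or higher, or about 21% or lower. At p = 0.80, h = 1.96 × √(0.16/100) = 0.0784, which rounds to 8%.

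**Retention, n = 100:**

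| Rate | 95% half-width (points) |
|---|---|
| 50% | 1.96 × √(0.25/100) = 9.80 |
| 60% | 1.96 × √(0.24/100) = 9.60 |
| 70% | 1.96 × √(0.21/100) = 8.98 |
| 75% | 1.96 × √(0.1875/100) = 8.49 |
| 80% | 1.96 × √(0.16/100) = 7.84 |

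The maximum, at 50%, is 9.80. The excess over the stated figure is 8.98 − 8 = 0.98 points at 70% and 9.80 − 8 = 1.80 points at 50%.

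**Does the choice of interval matter?** Half-widths in points with n = 100:

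| 95% method | at 70% | at 50% |
|---|---|---|
| Wald | 8.98 | 9.80 |
| Wilson | 8.84 | 9.62 |
| Clopper-Pearson | 9.37 | 10.17 |
| Wald, continuity-corrected | 9.48 | 10.30 |

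None of these gives 8 at either rate. A 90% Wald interval comes near (7.5 at 70%, 8.2 at 50%), but the article specifies 95%.

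**Size needed for ±8 points.** n = 1.96² × p(1 − p)/0.08² is 126.05 at 70% and 150.06 at 50%, so 127 and 151 after rounding up.

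**Recruitment.** If 100 consent at rate p, the denominator is 100/p, and h = 1.96 × √(p(1 − p)/(100/p)) = 1.96 × p × √((1 − p)/100). This is largest at p = 2/3: 1.96 × 0.667 × √(0.333/100) = 0.0754. At 50% (200 eligible) it is 6.93 points, and at 80% (125 eligible) 7.01 points. With 100 consenting, recruitment stays inside ±8 at every rate.

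**The case against.** The best defence is that ±8% is a correct figure whose assumption was left out. It reproduces at about 80% retention, planning precision is often quoted at the expected rate, and a journal article may leave that rate to the full protocol. That is a plausible origin, and it is why the figure should not be called a demonstrated miscalculation. It does not rescue the sentence as printed: the claim is unconditional, no 80% appears in the article, and the retention rates it does name are 50% and 70%.

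Four stronger readings are tempting, and the documents do not support them.

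- *That the claim fails for recruitment too.* The denominator is not the 100 randomised, but the correct one is larger if 100 consent, so ±8% is conservative there. The third Stop-Go bullet is worded as recruitment below 50%, and at that rate the half-width is 6.9 points. The 50% retention figure concerns only the lower edge of the middle band.
- *That the Stop-Go decision is undermined.* No bullet uses the ±8% or a confidence limit; each compares an observed rate with a cut-off. The correction also changes little. At an observed 70%, ±8 implies 62% to 78%, against about 61% to 79% by Wald or 60.4% to 78.1% by Wilson.
- *That the sample size rests on the ±8% and must rise.* Section 2.1 attributes the 100 to consultation and guidelines. The precision sentence describes what 100 delivers and is not shown to have determined it.
- *That retention per arm is misstated.* With 50 per arm the half-width at 70% is 12.7 points, but the protocol makes no per-arm precision claim and sets no per-arm criterion.

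It is also true that the final report is to carry the actual 95% intervals, so the planning figure will not distort the results.

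**Conclusion.** The point holds, and it is minor. For overall retention among 100 randomised participants, the unconditional ±8% is too favourable by about 1 point at 70% and about 1.8 points at 50%, and it is met only at rates of about 79% or higher (or 21% or lower). For recruitment the same figure is conservative, on the assumption that 100 people consent.

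The conclusion rests on reading the accuracy as the half-width of a two-sided 95% interval, as the adjoining sentence indicates, and on a retention denominator of 100. If retention is instead based on those who consented and slightly more than 100 consent, precision improves a little, but 127 would be needed to reach ±8 points at 70%. No analysis, decision rule or sample size is affected.

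**What to change.** Replace the precision sentence in section 2.4 with one that separates the two rates and gives the rate behind each figure, for example:

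> With 100 randomised, the 95% CI half-width for overall retention is at most about ±10 percentage points (±9.0 at 70%, ±7.8 at 80%). The recruitment rate is estimated on all eligible people referred, with a half-width of at most about ±7.5 points if 100 consent.

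If the ±8% was meant for an expected retention of about 80%, the smaller change is to state that rate beside it and add the value at 70%.

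The cost is one sentence and a slightly less favourable figure for retention. The sample size, the Stop-Go rule and the analysis stay as they are.
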